### **10.2.4 Safety analysis set (SAS)**

The SAS is defined as all registered subjects excluding those in whom dynamic chest radiography was not acquired even once.

Analysis populations will be finalised before database lock at a case review meeting. If issues not described here need to be considered for specific cases, the decision will be made at the case review meeting.

## **10.3 Analysis items and methods**

### **10.3.1 Primary analysis**

The primary analysis will be performed in the ITT population. This trial is designed to demonstrate superiority of the intervention. The null hypothesis is that the diagnostic accuracy of initial discrimination in the intervention group is less than or equal to that in the control group; the alternative hypothesis is that the diagnostic accuracy in the intervention group is greater than that in the control group.

A two-sided significance level of 5% will be used. The specific statistical test for the primary endpoint will be described in the statistical analysis plan.

### **10.3.2 Secondary and exploratory analyses**

Secondary and exploratory endpoint analyses will be performed as described in Section 5.7 Endpoints and rationale.

### **10.3.3 Safety analysis**

Adverse events and malfunctions will be summarised in the SAS.

### **10.3.4 Other analyses**

The same analyses as in the ITT population will also be performed in the FAS.

## **10.4 Handling of missing data**

Missing data will not be imputed. Analyses will be conducted based on available data.

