### **5.5 End of testing (EoT)**

Registered subjects will reach the end of testing (EoT) upon completion of dynamic chest radiography and V/Q scintigraphy. After the principal or subinvestigator determines the diagnosis of CTEPH versus non-CTEPH, all required information will be entered into the electronic data capture (EDC) system without omissions. Adverse events will be collected in relation to dynamic chest radiography. If a serious adverse event occurs, appropriate measures prioritising patient safety will be taken. In the event of discontinuation, the prespecified assessments at discontinuation will be performed as far as possible within 7 days, and the date and reason for discontinuation will be recorded. Serious adverse events will be reported appropriately in accordance with Section 8 (Adverse events and malfunctions).

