### 5.7.3 Exploratory endpoints

- Subgroup analyses in the primary endpoint according to sex (male vs female): comparison of accuracy, sensitivity and specificity between the group of the standard initial work-up alone versus the device -added group.

- Subgroup analyses in the primary endpoint according to obesity (BMI  $\geq 25$  kg/m^2 vs BMI  $< 25$  kg/m^2): comparison of accuracy, sensitivity and specificity between the group of the standard initial work-up alone versus the device -added group.

- Subgroup analyses in the primary endpoint according to pulmonary vascular resistance ( $> 4.0$  Wood units vs  $\leq 4.0$  Wood units): comparison of accuracy, sensitivity and specificity between the group of the standard initial work-up alone versus the device -added group.

- Subgroup analyses in the primary endpoint according to NT-proBNP ( $\geq 300$  pg/mL vs  $< 300$  pg/mL): comparison of accuracy, sensitivity and specificity between the group of the standard initial work-up alone versus the device -added group.

- Subgroup analyses in the primary endpoint according to peak tricuspid regurgitation velocity (greater than the median vs  $\leq$  the median): comparison of accuracy, sensitivity and specificity between the group of the standard initial work-up alone versus the device -added group.

- Subgroup analyses in the primary endpoint according to cardiac rhythm (sinus rhythm vs non-sinus rhythm): comparison of accuracy, sensitivity and specificity between the group of the standard initial work-up alone versus the device -added group.

- Subanalysis 1: comparison of accuracy, sensitivity, specificity, PPV and NPV between the control and intervention groups stratified by reader experience (more than 5 years vs 5 years or less) in the ITT population and in the full analysis set (FAS).

- Examination time (time spent in the examination room), radiation dose (dose area product [DAP], only in facilities able to measure it) and number of acquisitions including repeats when acquiring dynamic chest radiography for the pulmonary circulation analysis program in the ITT population and FAS.

- Exclusion proportion of pulmonary circulation analysis images reconstructed from dynamic chest radiography in the ITT population and FAS (including reasons for exclusion, e.g., failure to acquire dynamic chest radiography, failure of analysis by the program, or images judged inappropriate by investigators).

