## 10 Statistical considerations

### 10.1 Rationale for sample size determination

The diagnostic performance of V/Q scintigraphy is extremely high, with sensitivity and specificity reported as 90–100% and 94–100%, respectively. However, access to V/Q scintigraphy may be delayed and it is not available in many non-expert centres; therefore, adding the pulmonary circulation analysis program to the initial work-up is expected to improve early discrimination of CTEPH.

In the retrospective study conducted at Kyushu University Hospital (Section 1.5), the diagnostic performance of dynamic chest radiography/pulmonary circulation analysis for CTEPH discrimination was high (accuracy 0.92), whereas published data indicate limited diagnostic performance of static chest radiography alone. Based on these data, the expected accuracy for initial discrimination using the standard initial work-up alone is assumed to be approximately 0.705, and the expected accuracy when adding the pulmonary circulation analysis program is assumed to be approximately 0.92 (difference 0.215).

To detect an accuracy difference of 0.215 between the two groups with a two-sided significance level of 5% and 80% power under a 1:1 allocation, the required sample size is calculated as 102 cases (51 per group). Allowing for approximately 5% dropouts or non-evaluable cases, the target sample size was set at 108 cases (54 per group).

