### 10.2 Analysis populations

#### 10.2.1 Intention-to-treat (ITT) population

The ITT population is defined as all registered subjects excluding the following:

- Cases judged by the principal investigator to have difficulty in making a clear discrimination diagnosis of CTEPH versus non-CTEPH.
- Cases found after registration to not meet inclusion criteria or to meet exclusion criteria.
- Cases with major non-compliance with Good Clinical Practice (GCP).

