#### 10.2.2 Full analysis set (FAS)

The FAS is defined as the ITT population excluding the following:

- Cases in which any of the initial work-up tests (blood tests, static chest radiography, 12-lead ECG, or pulmonary function tests) were not performed, or cases with three or more missing items in blood tests.
- Cases without dynamic chest radiography images, or cases in which the image interpretation committee judges that appropriate dynamic chest radiography images required to perform the pulmonary circulation analysis program are not available (e.g., due to inadequate breath-hold or body motion).

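### The protocol gives no primary call for a device-arm case without a usable device image, and its available-data rule permits such cases to leave the device arm only

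*Protocol*

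**What the plan says.** **Population.** Protocol 10.3.1: "The primary analysis will be performed in the ITT population". Section 10.2.1: "The ITT population is defined as all registered subjects excluding the following". Three exclusions follow: no clear diagnosis, ineligibility found after registration, and major GCP non-compliance. Image availability is not among them. It enters at FAS level, where 10.2.2 removes "Cases without dynamic chest radiography images, or cases in which the image interpretation committee judges that appropriate dynamic chest radiography images required to perform" the analysis program are lacking. The alt-FAS (10.2.3) has the same exclusion.

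**Missing data.** Section 10.4: "Missing data will not be imputed. Analyses will be conducted based on available data".

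**The reading.** Under 7.1.6 a device-arm call rests on the initial work-up together with the program's output, with details left to the SOP for image interpretation. Section 13.2 adopts one reader's call per case from a table fixed in advance. Neither section covers a case whose analysis image is absent or rejected.

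**Timing.** Section 5.5: "Registered subjects will reach the end of testing (EoT) upon completion of dynamic chest radiography and V/Q scintigraphy". Section 5.6 allocates after EoT, the investigator's diagnosis and a check for missing EDC entries, and then describes creation of the analysis images. The schedule in 7.2 puts allocation and image reconstruction in one column. Under 10.2.2 the committee judges whether the images are adequate.

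**Failure reporting.** Section 5.7.3 lists as exploratory: "Exclusion proportion of pulmonary circulation analysis images reconstructed from dynamic chest radiography in the ITT population and FAS". The reasons it names include failed acquisition, failed analysis and images judged inappropriate.

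**The concern.** The protocol foresees image failures and keeps the affected cases in the primary set, but does not say how they are scored in the arm where the image matters. A control case with an unusable image is still read on the work-up and counts. If the same kind of case in the device arm is treated as having no result, 10.4 lets it fall out of the numerator and the denominator. The primary comparison would then set device cases with good images against all control cases. The FAS removes image failures from both arms, since every subject is meant to have DCR, so on this point the primary ITT comparison could be less balanced than the supporting one.

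Two related passages do not fit together. The ITT set starts from all registered subjects, and the FAS subtracts those without DCR, so the ITT set contains them. Yet allocation needs EoT, and EoT needs completed DCR. Read literally, a registered subject without DCR is in the ITT set but in no arm. In addition, the exclusion proportion is to be reported in the FAS, from which cases with missing or committee-rejected DCR have already been removed.

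**Working it through.** **Inputs (Protocol 10.1).** Control accuracy p0 = 0.705; device-arm accuracy p1 = 0.92; difference 0.215; two-sided 5%; 80% power; 1:1; 51 per group (102), raised to 54 per group (108) for about 5% losses.

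**Assumption.** The protocol gives no failure rate. Let f be the share of allocated device-arm cases without a usable analysis image, ranged from 2% to 20%. At 54 per group, f = 5% is 2.7 cases and f = 10% is 5.4.

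**Step 1: the plan's own figure.** With pooled variance, mean proportion (0.705 + 0.92)/2 = 0.8125:

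n = [1.96·√(2·0.8125·0.1875) + 0.8416·√(0.705·0.295 + 0.92·0.08)]² / 0.215² = 50.5, so 51 per group.

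102/0.95 = 107.4, so 108. Both stated figures reproduce.

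**Step 2: three ways to handle a failed image.**
- Dropped: accuracy 0.92 on 54(1 − f) cases.
- Read on the work-up alone: 0.92(1 − f) + 0.705f.
- Scored incorrect: 0.92(1 − f).

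At f = 5%, the work-up reading gives 0.874 + 0.03525 = 0.909, a difference of 0.204. Scoring as incorrect gives 0.874, a difference of 0.169.

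Power uses the same normal approximation, with 54 control cases and no other losses:

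| f | Dropped: difference (power) | Work-up alone: difference (power) | Scored incorrect: difference (power) |
|---|---|---|---|
| 2% | 0.215 (0.822) | 0.211 (0.806) | 0.197 (0.736) |
| 5% | 0.215 (0.814) | 0.204 (0.775) | 0.169 (0.579) |
| 10% | 0.215 (0.801) | 0.194 (0.719) | 0.123 (0.325) |
| 20% | 0.215 (0.770) | 0.172 (0.596) | 0.031 (0.055) |

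Relative to the two alternatives, dropping overstates the difference by 0.011 or 0.046 at f = 5%, and by 0.022 or 0.092 at f = 10%.

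**Step 3: no true device effect.** Suppose accuracy would be 0.705 if every case were read, and failed cases have accuracy q. The remaining device cases then have accuracy (0.705 − f·q)/(1 − f).
- q = 0.705: 0.705, so no bias.
- q = 0.60: +0.0055 at f = 5%, +0.0117 at f = 10%.
- q = 0.50: (0.705 − 0.025)/0.95 = 0.7158, or +0.011, at f = 5%; (0.705 − 0.05)/0.90 = 0.7278, or +0.023, at f = 10%.

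For scale, the standard error of the difference with 54 per arm and both accuracies 0.705 is √(2·0.705·0.295/54) = 0.088. The values of q are assumptions too.

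**The case against.** The strongest reply is that an unusable image is a missing input, not a missing outcome. The device-arm reader holds the whole work-up, one call is adopted per case, and 10.4 nowhere says that such a case goes unread. The existence of the FAS supports this: if 10.4 already dropped these cases from the ITT set, the FAS image exclusion would do little in the device arm. The reading SOP, which is not shown, may settle the matter. All of this stands against the stronger reading that a reader might infer, namely that 10.4 does remove failed cases. It does not answer the point that the protocol leaves both readings open while fixing an available-data rule for the primary set.

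Three further inferences are tempting but unsupported:
- That the 5% allowance in 10.1 shows an intention to drop image failures. It applies to both groups, does not mention images, and fits the three ITT exclusions equally well.
- That the exclusion proportion in the FAS must be zero. Cases with missing or committee-rejected DCR are gone, but a program failure on an adequate DCR is not excluded by the wording of 10.2.2.
- That failed cases are harder to classify. This is plausible where breath-hold fails, but the protocol offers no evidence for it.

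It is also fair that technologists check and repeat poor acquisitions (5.3.1), and that losses before allocation fall on both arms. The mismatch over registered but unallocated subjects therefore does not itself favour the device. Only failures that surface after allocation, such as program failure or committee rejection, can produce a one-sided loss, and the shared column heading in the schedule does not fix the order of allocation and image creation.

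**Conclusion.** The concern holds as a gap in the primary analysis rule. Cases with missing or unusable device images belong to the primary ITT set, no primary call is specified for them in the device arm, and 10.4 permits their loss from that arm alone. If that happened, the estimate would move in the device's favour, by the amounts in the table. Those amounts rest on an assumed failure share, on the protocol's accuracies of 0.705 and 0.92, and on failures being unrelated to difficulty when a true effect exists. With no true effect and failed cases of average difficulty, the bias is zero.

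The lower power under the other two rules reflects a smaller target difference and is not evidence of bias. It does show that a choice left open matters: at f = 5%, power is 0.814, 0.775 or 0.579 depending on the rule. The documents do not establish that failures will be dropped or how often they will occur.

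**What to change.** 1. In 10.2.1, 10.4 and 13.2, state that every allocated case receives a scored primary reading in its own arm. A device-arm case without a usable analysis image is read on the initial work-up alone, and that call counts.
2. Add a sensitivity analysis that scores such cases as incorrect.
3. Reconcile the ITT definition with 5.5 and 5.6, for example by defining the primary set as all allocated cases with the exclusions already listed, and account separately for registered subjects who were never allocated.
4. In 5.7.3, report image failures, with reasons, over all registered subjects with attempted DCR.

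The cost is protocol, SAP and SOP wording, and a few work-up-only readings: about 3 cases at f = 5%, or 5 to 6 at f = 10%. The device estimate becomes slightly less favourable, and planned power falls to 0.775 or 0.719 at those shares. The sponsor should weigh that before reading starts.

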## **10.5 Multiplicity adjustment**

No multiplicity adjustment will be performed.

## **10.6 Interim analysis**

No interim analysis is planned.

# **11 Study completion or termination**

## **11.1 Study completion**

After all trial procedures have been completed for all subjects, the principal investigator will submit a written report to the head of the implementing medical institution stating that the trial has been completed and providing an outline of the trial results. The head of the implementing medical institution will promptly notify the institutional review board (IRB) in writing of the completion of the trial, and will report an outline of the trial results based on the report submitted by the principal investigator.

## **11.2 Study termination**

### **11.2.1 Termination criteria**

- If the coordinating investigator judges that the trial should not be continued (e.g., serious adverse events or malfunctions related to the investigational device).
- If ethical or scientific issues are identified in the trial.
- If a termination recommendation is issued by the IRB or the regulatory authority.

### **11.2.2 Procedures in the event of termination**

If any matter corresponding to the termination criteria occurs, the coordinating investigator and the principal investigator will immediately consult and decide whether to terminate the trial. If the decision is made to terminate the trial, the coordinating investigator will, as necessary, communicate the reason for termination and subsequent actions in writing to the head of the implementing medical institution, the IRB and other stakeholders. Appropriate measures will be taken to ensure subject safety and to manage any required follow-up.

# **12 Data handling**

## **12.1 Creation or modification of case report forms**

The principal investigator, subinvestigators or study staff will promptly create or modify case report forms using the EDC system in accordance with the data entry manual. Data recorded in the case report forms that are derived from source documents must not contradict the source documents. If inconsistencies exist between source documents and case report forms, the reason must be explained. The principal investigator must ensure that the data in the case report forms and all other reports are accurate and complete. The principal investigator will confirm the appropriateness of the completed case report forms and provide an electronic signature.

## **12.2 Definition of the original case report form**

The original case report form is defined at each stage of creation and storage of electronic data as follows:

- During the trial, all electronic data entered directly into the EDC system are regarded as the original. The EDC system storing the original data will be appropriately backed up to prepare for disasters, system failures, etc.
- After trial completion, all electronic data for the trial will be transferred from the EDC system to optical recording media, which will be regarded as the original. A duplicate will be created as a copy. Thereafter, all electronic data for this trial stored on the EDC server will be invalidated.

## **12.3 Source documents**

In this trial, source documents include the following:

- Records related to the subject's informed consent and provision of information.
- Materials that serve as the basis for entries in case report forms, such as medical records, nursing records, CT images and X-ray images.
- Records related to investigational device management.

For the following items that are entered only into the case report forms, the case report forms will be regarded as the source documents:

- Medical history, comorbidities, concomitant medications, concomitant therapies, and presence/absence of malfunctions.
- Comments and findings, etc.

## **12.4 Handling of withdrawal of consent**

If a subject withdraws consent, the investigator will confirm whether the subject permits continued use of data that have already been collected. If the subject does not permit use of the data, the collected data will be deleted in accordance with applicable procedures and will be excluded from analysis. Details of the subject's decision will be recorded in the medical record.

# **13 Image interpretation committee**

## **13.1 Composition**

The image interpretation committee will perform independent image evaluations for the purpose of determining the outcomes. Committee members will be selected based on their experience with pulmonary hypertension and CTEPH. In order to maintain independence, physicians performing primary endpoint interpretations will be internal medicine physicians who have not been working full-time at a CTEPH expert centre, which is certified by the

Japanese pulmonary circulation and pulmonary hypertension society, in the past three years.

For interpretation of perfusion scintigraphy images used in the six-region regional perfusion defect assessment, nuclear medicine physicians (or radiologists with expertise in nuclear medicine) who are working at a CTEPH expert centre within the past three years will be selected.

### **13.2 Determination of CTEPH/non-CTEPH in the primary endpoint**

For the primary endpoint, five internal medicine physicians will perform the initial discrimination between CTEPH and non-CTEPH in each reading group (standard initial work-up group and standard initial work-up plus pulmonary circulation analysis program group). The five readers in each group will include three readers with more than five years of experience in CTEPH diagnosis and two readers with five years or less of experience.

For the primary endpoint, the adopted interpretation will not be decided by a simple majority vote. Instead, a prespecified correspondence table will be created in advance such that a single reader's judgement is uniquely adopted for each case. Readers will not be informed of which cases constitute the primary endpoint analysis set.

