### **13.3 CTEPH/non-CTEPH determination in the secondary endpoint (pulmonary circulation analysis program images)**

For one secondary endpoint, the same five readers as in the primary endpoint will interpret dynamic chest radiography/pulmonary circulation analysis images in the intervention group to determine CTEPH/non-CTEPH. In this evaluation, the determination will be made by majority vote among the five readers.

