### **13.4 Determination of regional perfusion defects (six-region assessment)**

For the six-region assessment, each lung is divided into upper, middle and lower regions (six regions in total). Each region will be assessed for the presence or absence of a perfusion defect on pulmonary circulation analysis images and on perfusion scintigraphy images.

Pulmonary circulation analysis images will be interpreted by the same five internal medicine physicians as in the intervention group. Perfusion scintigraphy images will be interpreted by three nuclear medicine physicians from CTEPH expert centres. All designated readers will interpret all cases. The final presence/absence of a regional perfusion defect for each region will be determined by majority vote.

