### **13.5 Reader training**

Prior to the start of image interpretation, readers will undergo training on how to interpret pulmonary circulation analysis images. After training, each reader will perform a test interpretation to confirm that the reader has acquired the necessary interpretation skills. The committee will evaluate inter-reader variability of pulmonary circulation analysis images.

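### Sections 13.2 and 13.4 point to a separate five-reader panel per group, which would mix the device effect with panel differences that the sample size does not allow for

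*Protocol*

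**What the plan says.** Section 5.6 randomises cases 1:1 to the two reading groups, stratified by final diagnosis. It describes no random assignment of readers to groups.

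Section 13.2 says that "five internal medicine physicians will perform the initial discrimination between CTEPH and non-CTEPH in each reading group". It sets the experience mix group by group: "The five readers in each group will include three readers with more than five years of experience in CTEPH diagnosis", the other two having five years or less. The primary endpoint uses no vote; instead, "a prespecified correspondence table will be created in advance such that a single reader's judgement is uniquely adopted for each case".

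Two later sections refer back to these readers in different ways:
- Section 13.3, on the secondary endpoint: "the same five readers as in the primary endpoint will interpret dynamic chest radiography/pulmonary circulation analysis images in the intervention group".
- Section 13.4, on the six-region assessment: "Pulmonary circulation analysis images will be interpreted by the same five internal medicine physicians as in the intervention group". It adds that every designated reader reads every case.

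On training, section 13.5 says that "readers will undergo training on how to interpret pulmonary circulation analysis images" and then take a test reading. It does not limit this to one group.

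Section 10.1 sizes the trial on accuracies of 0.705 (work-up alone) and 0.92 (device added), two-sided 5% significance and 80% power. Section 10.3.1 leaves the primary test to the SAP.

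**The concern.** Randomising cases balances patients between groups. It does nothing for readers. If each group has its own five readers, the primary contrast is the device effect plus the difference in skill and decision threshold between two small panels. Because one reader's call is adopted per case, individual differences enter the endpoint without being averaged by a vote.

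Two things are at stake. A positive result could partly reflect a better panel. And calls by the same reader are correlated, so the cases in a group carry less information than the same number of independent observations, which is how the sample size treats them. A reader model in the SAP could widen the standard error, but with readers nested in group it could not separate panel from device. The assignment is fixed in protocol section 13.2, so it has to be put right there.

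**Working it through.** **Step 1. How many panels?** Three wordings bear on this.
- Section 13.2 gives the 3+2 mix for the readers of each group. That is natural only if each group has its own five.
- Section 13.4 identifies its readers by their membership of the intervention group. With one shared panel that would single out nobody.
- Section 13.3 speaks of five readers for the primary endpoint as a whole. That fits one shared panel, or loosely the intervention panel.

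Two of the three favour separate panels. None says whether five or ten people read.

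**Step 2. Reproduce the sample size.** Inputs from section 10.1: p1 = 0.705, p2 = 0.92, difference 0.215, mean 0.8125.

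n = [1.96·√(2·0.8125·0.1875) + 0.8416·√(0.705·0.295 + 0.92·0.08)]² / 0.215²
= (1.0819 + 0.4466)² / 0.046225 = 50.5, so 51 per group and 102 in total.

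102 / 0.95 = 107.4, so 108. This matches the protocol exactly, so the formula contains no reader term. The same formula gives power 0.804 at 51 and 0.826 at 54 per group.

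**Step 3. Size of a panel difference.** The protocol gives no reader variance. Assume that true accuracy has SD s = 0.05 to 0.10 between readers. For two panels of five:

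SD of the panel difference = √(2s²/5) = 0.032 (s = 0.05) to 0.063 (s = 0.10), a 95% range of about ±6 to ±12 points.

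For comparison, the observed difference that just reaches significance at 54 per group is about 1.96·√(2·0.8125·0.1875/54) = 0.147, or 15 points.

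**Step 4. Type I error of a test that ignores readers, separate panels.** Assume adopted reads are spread evenly: 54/5 = 10.8 per reader.

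Variance per group = p(1−p)/54 + s²(1/5 − 1/54).

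| s | p | Design effect | Two-sided type I error |
|---|---|---|---|
| 0.05 | 0.705 | 1.12 | 0.064 |
| 0.05 | 0.81 | 1.16 | 0.069 |
| 0.10 | 0.705 | 1.47 | 0.106 |
| 0.10 | 0.81 | 1.64 | 0.126 |

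Worked line: 0.705·0.295/54 = 0.00385; 0.0025·0.1815 = 0.00045; ratio 1 + 0.00045/0.00385 = 1.12; 1.96/√1.12 = 1.85, which gives about 0.064.

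**Step 5. Power of a reader-adjusted z test, separate panels, 54 per group.** The same model in terms of the within-reader correlation ρ (assumed equal in both groups) has design effect 1 + 9.8ρ.

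| ρ | Reader SD at p = 0.705 | Design effect | Power | Evaluable cases per group for 80% |
|---|---|---|---|---|
| 0 | 0 | 1.00 | 0.83 | 51 |
| 0.01 | 4.6 points | 1.10 | 0.79 | 57 |
| 0.02 | 6.4 points | 1.20 | 0.75 | 63 |
| 0.05 | 10.2 points | 1.49 | 0.66 | 99 |

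The last column solves n = 51(1−ρ)/(1 − 51ρ/5). At ρ = 0.10 the denominator is negative, so no number of cases is enough with five readers per group.

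**Step 6. Separate against shared panels.** A beta-binomial simulation (200,000 runs, 54 cases per group, true accuracy 0.705 in both groups, unadjusted two-proportion z test) gave a two-sided type I error of 0.061, 0.072 and 0.108 for separate panels at ρ = 0.01, 0.02 and 0.05. With the same five readers in both groups and near-equal caseloads it stayed at 0.042 to 0.049 for ρ from 0.01 to 0.10. The inflation comes from nesting readers in group.

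**The case against.** **Separate panels are inferred.** No sentence says that there are ten readers or that the panels are different people, and section 13.3 fits one panel of five. The reader-study figure and the reading SOPs, which might settle it, were not available for this review. This stands. The point is therefore conditional, but the trial's only confirmatory comparison should not depend on an ambiguity.

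**Training.** A reader might infer that only the device panel is trained, so that training is confounded with group. Section 13.5 speaks of readers in general, so the protocol does not support this.

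**The error rate.** A reader might infer that the nominal 5% fails. That follows only if the primary test ignores readers. The test is left to the SAP, which is not at hand and may model them. What the SAP cannot do is undo the nesting.

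**The size is assumed.** The reader SD is not in the protocol. If s is the total SD, the figures in steps 3 and 4 are upper bounds, because the matched 3+2 mix removes the part due to experience. At 5 points the inflation is modest. All of this stands.

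**Separate panels have a use.** Sections 5.6, 10.2.3 and 13.4 together have the intervention group's readers see device images of control-group cases for the six-region read. If they also made control-group calls, they could already have seen the device image of the same case. Crossing readers is therefore not free of a recall problem, and the visible text fixes no reading order. This is a real cost, met by fixing the order.

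**Conclusion.** The point holds in conditional form. The natural reading of sections 13.2 and 13.4 is one panel per group. On that reading the device effect cannot be told apart from panel differences, and the sample size makes no allowance for readers. The stated 51, 102 and 108 are arithmetically correct for independent reads, so it would be wrong to conclude that the calculation itself is in error.

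For an assumed between-reader SD of 5 to 10 points and evenly spread adopted reads, a test that ignores readers has a two-sided type I error of about 6% to 13%. A reader-adjusted test at 54 per group falls below 80% power over much of that range, to about 66% near its top. A panel difference of this size would be unlikely to account for the whole planned 21.5 points. It could, however, supply much of the roughly 15 points needed for significance. If one panel of five serves both groups with equal caseloads, the inflation disappears and only the wording needs repair.

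**What to change.** Amend section 13.2 before reading starts:

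1. State how many primary-endpoint readers there are and that each reads cases from both groups. With ten readers in two sets of 3+2, each set could read half the control cases and half the device cases. Every case keeps five reads, and each reader keeps 27 + 27 = 54 cases.
2. Balance adopted reads by reader and group in the correspondence table.
3. State in section 13.5 that all primary-endpoint readers receive the same training and test reading.
4. Block or stratify the primary comparison by reader, and carry this into the SAP.
5. Require each reader to complete and lock all primary reads before seeing device images of control-group cases for the section 13.3 and 13.4 assessments.
6. Align the references to five readers in sections 13.3 and 13.4.

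The cost is a change to the protocol text, the correspondence table and the reading SOP, with the same number of readers and primary reads. There are two downsides: control reads are made by readers trained on device images, and the reading order has to be managed. Once reading is done with separate panels, analysis cannot repair the confounding.
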